### Data Analysis

Data will be analyzed on an intention-to-treat (ie, participants analyzed on the basis of their group allocation regardless of whether they received the intended treatment), and per protocol basis (participants analyzed on the basis of their group allocation and receiving the intended treatment). Descriptive statistics will be presented and baseline variables will be compared between groups to test for fairness with respect to the randomization. Aim one (primary outcome) will be tested using test of proportions and logistic regression to control for potentially confounding factors. Changes in health utility and COHRQoL (secondary outcomes) will be tested using paired (within group) and unpaired (between groups) and parametric and nonparametric tests as appropriate, and multivariate analysis using linear regression for continuous variables and Poisson regression for count variables to control for possible intergroup imbalances. Responsiveness of the COHRQoL scale will be determined by calculation of effect sizes for the scale overall and specific domains. Statistical significance will be set at alpha=.05. All analyses will take into account the cluster design and will incorporate multilevel analyses where indicated. Multiple imputation of missing data will be further undertaken to evaluate its impact on the primary and secondary outcomes.

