### Aims

The principal aim of the proposed study is to develop, implement, and evaluate a remote primary care model to deliver effective primary dental services, encompassing treatment and preventive services, to Aboriginal preschool children (based on minimally invasive approaches including ART). This will be compared with standard care for cost and benefits in terms of improved dental health and reduced childhood dental anxiety. Our specific aims and hypotheses are:

Aim 1. Measure the proportion of children able to be provided with care without the need for dental specialist referral and the increment in dental caries. Hypothesis: The proportion of children successfully managed without specialist referral and without new dental caries will be higher in the test group compared with the control.

Aim 2. Develop a dental-specific health utility scale and measure the change in childhood health utility. Hypothesis: The change in health utility will be greater in the test group compared with the control.

Aim 3. Undertake an economic evaluation of the intervention. Hypothesis: The test intervention will have either less costs with greater/similar health gain or affordable incremental costs for additional unit of health outcomes.

Aim 4. Measure the change in childhood oral health-related quality of life. Hypothesis: The child oral health-related quality of life in the test group will be better than the control

Aim 5. Evaluate the acceptability of the ART-based care through focus group interviews. Hypothesis: The ART-based care will have greater acceptability than the control.

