### Outcomes

Primary outcomes are specialist referral and the increment in dental caries. Secondary outcomes are quality of life and acceptability of the ART-based care.

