### Treatment Procedures

Test children will be provided with care by dental therapists previously trained in and using the ART approach. Treatment will be undertaken at SDS clinics or field settings, using portable equipment. Restorative treatments will be provided using hand instruments principally, without the use of local anesthesia with the cavity prepared and subsequently restored with a glass-ionomer cement. Where extractions are required, the procedure will be undertaken using standard care approaches. All children will also be provided with preventive fluoride varnish applications at treatment and reviewed at 6-month follow-ups. All treatment will be recorded in patient clinic records. At the 6-month reviews, participants will be provided with preventive fluoride varnish and any other necessary care. Children unable to be provided with care will be referred for specialist care. There will be no direct costs incurred by the participants for the primary care.

Control children will be provided with standard care as part of the fluoride varnish program. Children found to require dental treatment will be referred for care through the prevailing care pathway, that is, government dental services or local private practitioners.

In order to ensure all participants are offered the opportunity to access dental treatment, and in keeping with the delayed treatment intervention design, control participants will be offered treatment using the test treatment approach after the 12-month follow-up.

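### As worded, the per-protocol set can drop test children because they were referred, so it can select on a primary outcome in the test arm only

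*Protocol article*

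**What the plan says.** Data Analysis lists two analysis sets side by side. Under intention-to-treat, children are "participants analyzed on the basis of their group allocation regardless of whether they received the intended treatment". The other is a "per protocol basis (participants analyzed on the basis of their group allocation and receiving the intended treatment". The section does not say which is primary.

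The Outcomes section states: "Primary outcomes are specialist referral and the increment in dental caries". Aim 1 is worded in the same direction: "Measure the proportion of children able to be provided with care without the need for dental specialist referral and the increment in dental caries".

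Treatment Procedures describes the arms differently.

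- **Test arm:** "Test children will be provided with care by dental therapists previously trained in and using the ART approach". Specialist referral follows when this fails: "Children unable to be provided with care will be referred for specialist care".
- **Control arm:** "Control children will be provided with standard care as part of the fluoride varnish program". Onward referral for ordinary treatment belongs to that pathway: "Children found to require dental treatment will be referred for care through the prevailing care pathway, that is, government dental services or local private practitioners".

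**The concern.** In the test arm, getting the intended care and avoiding specialist referral are close to being the same event. Restricting the set to children who got the intended care can therefore remove children because they had the outcome being compared. The control arm has no matching step: its intended care is the varnish program plus the usual pathway, and being referred is nowhere described as a departure from it.

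Most per-protocol selection has an uncertain direction. Here the direct effect runs one way, because removing referred children from the test arm lowers its referral rate. Shown beside the intention-to-treat result with no stated order between them, the per-protocol comparison could be read as support for a benefit that the selection itself had produced or enlarged.

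**Working it through.** **Inputs (Sample Size section).** Referral 10% test versus 25% control; intracluster correlation 0.05; 15 clusters per arm; 80% power; alpha 0.05 (taken as two-sided, which the article does not state); 165 per arm, 11 per cluster; 220 per arm after 25% loss.

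**The plan's own figure.** With a fixed number of clusters, m = n(1 − ICC)/(k − n·ICC). The pooled two-proportion formula with t quantiles on 28 df gives n = 106.9 per arm under individual randomization. Then m = 106.9 × 0.95/(15 − 106.9 × 0.05) = 10.52, rounded up to 11, and 15 × 11 = 165. For loss, 165/0.75 = 220. Both figures reproduce, so the sample size is not in question. The design effect is 1 + (11 − 1) × 0.05 = 1.5.

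**Effect of the per-protocol rule.** Let p be the true test-arm referral rate and f the share of referred test children excluded, with no control child excluded for being referred. The per-protocol test rate is

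p(1 − f)/(1 − p·f).

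The value of f is an assumption, so a range is shown. The chance of a significant result favouring test uses the two-proportion normal approximation, with numbers per arm divided by 1.5.

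*No true effect, 25% in both arms:*

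| f | Per-protocol test rate | Control | Difference (points) | Chance of significance favouring test |
|---|---|---|---|---|
| 0 | 25.0% | 25% | 0 | 2.5% |
| 0.25 | 0.1875/0.9375 = 20.0% | 25% | 5.0 | 14% |
| 0.5 | 0.125/0.875 = 14.3% | 25% | 10.7 | 48% |
| 0.75 | 0.0625/0.8125 = 7.7% | 25% | 17.3 | 91% |
| 1 | 0/0.75 = 0% | 25% | 25.0 | about 100% |

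Worked line for f = 0.5. The test arm keeps 165 × 0.875 = 144.4 children, an effective 96.25; control has 165/1.5 = 110. The pooled rate is (96.25 × 0.1429 + 110 × 0.25)/206.25 = 0.20. The standard error is 0.0558 under the null and 0.0546 under the alternative. Then (0.1071 − 1.96 × 0.0558)/0.0546 ≈ −0.04, a probability of about 0.48.

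*No true effect, 10% in both arms:* the chance is about 9%, 25%, 58% and 92% at f = 0.25, 0.5, 0.75 and 1.

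*Planned effect, 10% versus 25%:* the intention-to-treat difference is 15 points. Per protocol, f = 0.5 gives 0.05/0.95 = 5.3% versus 25%, a difference of 19.7 points. With f = 1 it is 0% versus 25%, a difference of 25 points.

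**The case against.** Four points can be made against this.

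1. *Referral is a written step of the test pathway.* Test care is a package: therapist treatment, fluoride varnish, 6-month review and, where care cannot be provided, referral. A child who had varnish or some ART-based care before referral could be counted as having had the intended treatment. This stands. A reader might infer that the rule removes every referred test child by definition, and so favours ART whatever the truth. The article does not support that: it does not define intended treatment further, and f = 1 is only the strict reading. But nothing in the text secures f = 0 either, and any f above 0 lowers the test rate.

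2. *The control-arm wording concerns a different referral.* The pathway named for control children leads to government or private dental care, not to a specialist. That a control child later sent to a specialist stays in the set is therefore an inference. It is a fair one, because no wording makes such a referral a departure from standard care. Control children might be excluded for missing standard care, but that is not the same as being excluded for the outcome.

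3. *Intention-to-treat is planned, and an analysis plan may rank the sets.* Intention-to-treat is correctly defined, listed first and untouched by this point, so a claim that the trial has no sound comparison would be wrong. The absence of a ranking would not be a finding by itself. The point here is a rule that the article does state, and a later document that repeated it would carry the same problem.

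4. *Other endpoints behave differently.* The Aim 1 hypothesis joins freedom from referral with freedom from new caries. On that combined endpoint, dropping referred children would not bring test-arm failures to zero. Caries increment is not mechanically altered; it is touched only because the test children who remain may be the easier ones to treat. Both limits stand, and the figures above apply to referral alone.

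**Conclusion.** The point holds for the per-protocol comparison of specialist referral. Read together, Data Analysis and Treatment Procedures allow membership of the set to depend on that outcome in the test arm only, with a direct bias toward ART-based care for any f above 0. With no true effect at 25% in both arms, the spurious difference runs from 5 points (f = 0.25) to 25 points (f = 1), and the chance of a false significant result in that direction from about 14% to about 100%, against 2.5% without the selection. At f = 0 there is no bias.

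The size rests on f, which the article does not give; on no control child being excluded for referral; on 165 analysed per arm before exclusions; and on a design effect held at 1.5. The normal approximation is rough when the test rate is near 0%, but the conclusion there does not depend on it.

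**What to change.** Amend the Data Analysis paragraph before outcome data are examined:

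- Name intention-to-treat as the primary analysis.
- For the referral outcome, state that test children referred because care could not be provided remain in the per-protocol set and count as events.
- Exclude children only for departures that are unrelated to referral and can be applied equally in both arms, such as receiving the other arm's care. Attendance at a study treatment visit would not serve: the Recruitment section arranges such appointments only for the early treatment group, so that criterion would add a test-only selection of its own.
- Alternatively, drop the per-protocol analysis for referral.

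The cost is a few sentences, with no new data and no change to sample size or conduct. Timing matters, because deciding afterwards which referred children had received the intended care would be open to choices driven by the results.

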Participating communities, stratified by size of community (ie, number of children in the sample frame) and baseline dental caries experience, will be randomly assigned using a computer-generated block randomized list into immediate (test group) or delayed intervention (control group, given standard care) by a central study coordinator. We will select communities for recruitment based on available information on community population from various sources (eg, Community CEOs, the WA Country Health Service, Australian Bureau of Statistics). Communities will also be far enough apart to minimize contamination of test and control (at least 50 km). We will invite participation from communities with at least 100 people to ensure likelihood of recruiting at least 15 children in the age group of interest. We will stratify the communities on size of population and dental caries experience (high vs low; data obtained at baseline examination). Parents of all children of eligible age will be provided with information and consent forms and a questionnaire to complete (Aboriginal research assistants will explain the study to the parents and help parents complete the questionnaires). After receipt of signed consent, participants in the randomized study will be contacted for a baseline clinical examination by a calibrated examiner. After baseline examination, all participants will be contacted by the trial coordinator and appointments arranged for those allocated into the early treatment group. Test group participants will subsequently be contacted and appropriate appointments coordinated to be seen at the local SDS clinics or field clinic settings for treatment. Control group participants will be provided with standard preventive care by the Aboriginal Health Workers and managed for treatment as per standard procedures.

Study participants will be reviewed after 12 months from baseline and will undergo a clinical examination and complete a follow-up questionnaire. Figure 1 shows the study’s participant flow chart.

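### Communities are randomised within size and caries strata, but the analysis text does not commit to the strata or the baseline score as covariates, and it tests baseline balance instead

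*Protocol article*

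**What the plan says.** On design, the Recruitment section of the protocol article states "We will stratify the communities on size of population and dental caries experience (high vs low; data obtained at baseline examination"). Within those strata, communities are "randomly assigned using a computer-generated block randomized list into immediate (test group) or delayed intervention". The Methods part of the abstract gives the same two stratification factors.

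On analysis, the Data Analysis section makes four statements that bear on this point:

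- Baseline: "baseline variables will be compared between groups to test for fairness with respect to the randomization".
- Primary aim: "Aim one (primary outcome) will be tested using test of proportions and logistic regression to control for potentially confounding factors".
- Secondary outcomes: "Changes in health utility and COHRQoL (secondary outcomes) will be tested using paired (within group) and unpaired (between groups"), by parametric or nonparametric methods.
- Regression for the secondary outcomes: "linear regression for continuous variables and Poisson regression for count variables to control for possible intergroup imbalances".

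The section also says that every analysis will allow for the cluster design, with multilevel models where needed. Community size and the caries stratum do not appear in it, and neither does the baseline score as a covariate.

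**The concern.** Stratifying the allocation and then analysing without the strata leaves part of the benefit unused. Stratified allocation removes between-stratum variation from the true variance of the arm difference, but an analysis without the strata still counts it in the estimated standard error. The interval is then too wide and the test too cautious. A simple test of proportions has no place for covariates. Allowing for the cluster design deals with correlation within communities, which is a different matter from the strata.

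The baseline test of fairness asks whether differences between randomised groups could be due to chance. If the randomisation was done properly, they are. A significant result is then a false alarm, and a non-significant one does not show that a prognostic factor is balanced.

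For ECOHIS and the utilities, a test on the change gives the baseline value a fixed coefficient of 1. Using it as a covariate lets the data set the coefficient and is more precise whenever r is below 1. Paired tests within an arm do not address the between-arm hypotheses of Aims 2 and 4.

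What is at stake is precision and a clearly fixed estimate in a trial with few clusters. False-positive risk is not the issue.

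**Working it through.** **1. The plan's own figure.** The Sample Size section gives 10% vs 25%, intracluster correlation (ICC) 0.05, 15 clusters per arm, 80% power, alpha .05 (taken as two-sided), 11 children per cluster and 165 per arm.

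- Design effect: 1 + (11 − 1) × 0.05 = 1.50.
- Pooled proportion 0.175, so p(1 − p) = 0.144375.
- Standard error: √(2 × 0.144375 × 1.50 / 165) = 0.0512.
- Noncentrality: 0.15 / 0.0512 = 2.93. On t with 28 df, power is 80.7%.
- With 10 per cluster, power is 78.3%, so 11 is the smallest size that reaches 80%.
- Loss to follow-up: 165 / 0.75 = 220, and 11 / 0.75 = 14.7, rounded up to 15.

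The stated size reproduces. It contains no term for the strata.

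**2. What the strata are worth for specialist referral.** Let R² be the share of between-community variance that the strata explain. The documents do not give it, so 0 to 0.75 is assumed. A cluster-level simulation used 30 communities in four strata (8, 8, 8 and 6), allocation balanced within each stratum, 11 children per community, a standardised effect of 0.15 / √0.144375 = 0.395, and 6,000 runs per setting. It was analysed with and without stratum terms.

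| R² | Power without strata | Power with strata | Type I error without | Type I error with |
|---|---|---|---|---|
| 0 | 81.1% | 80.8% | 5.2% | 5.0% |
| 0.25 | 81.4% | 83.9% | 3.9% | 5.1% |
| 0.50 | 81.6% | 86.9% | 3.5% | 5.5% |
| 0.75 | 84.1% | 91.2% | 2.2% | 5.1% |

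The gains are −0.3, 2.5, 5.3 and 7.1 points. The −0.3 is within simulation error, since √(0.8 × 0.2 / 6000) is about 0.5 points.

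A closed-form check uses design effect 1 + (m − 1) × ICC × (1 − R²), where m = 11 is the number of children per cluster. This falls from 1.50 to 1.375, 1.25 and 1.125. With 26 df (two binary factors assumed), power is 80.5%, 83.7%, 87.0% and 90.2%, in line with the simulation.

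**3. With the communities agreed so far.** The Results section reports 26 communities, against the 30 in the sample size. Assume an even split of 13 per arm with 11 children each, giving 143 per arm. The standard error is √(2 × 0.144375 × 1.50 / 143) = 0.0550, the noncentrality 2.73, and power on 24 df about 74%. With strata on 22 df, power is about 78%, 81% and 85% for R² of 0.25, 0.50 and 0.75. If R² is 0, the two degrees of freedom cost about 0.3 points.

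**4. Change score against baseline adjustment.** Assume equal variance σ² at both times and correlation r.

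- Variance of a change: 2σ²(1 − r).
- Variance after baseline adjustment: σ²(1 − r²).
- Ratio: (1 − r²) / [2(1 − r)] = (1 + r)/2.

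For r = 0.3, 0.5 and 0.7 the ratio is 0.65, 0.75 and 0.85. Put the other way, the change-score variance is 1/0.65 = 1.54 times to 1/0.85 = 1.18 times the adjusted one. The documents give no r. Table 1 shows ECOHIS, CHU_9D, EQ-5D-Y and child dental fear collected at baseline and at follow-up, so the ratio can apply to these. It cannot apply to specialist referral.

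**The case against.** The strongest reply is that much of this rests on silence. A journal article may leave the covariate list to a full protocol or analysis plan that is not shown, and community size and caries could be among the potentially confounding factors it mentions. That stands: the strata are unmentioned, not excluded.

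A reader might infer that covariates will be picked from the results of the fairness tests. The comparison and the adjustment sit near each other in the section, but no rule connects them, so that charge is not supported.

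A reader might also take the paired tests as evidence for the arm hypotheses. The article does not say so. Between-group tests are planned alongside them, and within-person comparisons also suit its stated interest in scale responsiveness and response shift.

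The secondary outcomes get regression as well as tests on change, and nothing bars the baseline value from those models. Specialist referral and acceptability have no baseline value. Chance imbalance in caries is limited by the stratification itself, so it should not be presented as likely to matter.

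One could defend baseline comparisons in a cluster trial as a check on selective recruitment after allocation. A descriptive table serves that purpose without p-values. Here the caries stratum comes from the baseline examination, which implies that examination precedes allocation.

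What the reply does not remove is what the text states: the fairness test, a test of proportions that cannot carry the strata, tests on change scores, and adjustment justified by imbalance instead of by the design.

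**Conclusion.** The point holds as a mismatch between a stratified design and an analysis text that does not commit to using it. It should be corrected, but it does not threaten validity. A reader might suppose that omitting the strata inflates false positives. The reverse is true: simulated type I error without them was 2.2% to 5.2%.

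For specialist referral the loss is about 0 to 7 points of power for R² from 0 to 0.75, and nil if the strata do not predict referral. For ECOHIS, the utilities and child dental fear, baseline adjustment would cut the variance by 15% to 35% relative to change scores for r from 0.7 to 0.3. Both R² and r are assumptions, so the direction is firm and the size is not. The variance ratio also assumes equal variance at baseline and follow-up.

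**What to change.** Revise the Data Analysis section as follows.

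1. Make the primary between-arm analysis one cluster-adjusted model that includes the two stratification factors, community size and caries stratum. Keep any test of proportions as supportive.
2. Analyse ECOHIS, CHU_9D, EQ-5D-Y and dental fear as the follow-up value, with the baseline value and the strata as covariates and a community effect.
3. Present baseline variables by arm descriptively, without significance tests.
4. State that within-group tests are descriptive and do not bear on the arm hypotheses.

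The cost is wording only, because the strata and baseline scores are already collected. The downside is a few cluster-level degrees of freedom. With two binary factors that is 2 of 28 at 30 communities, or 2 of 24 at 26. Only caries is stated to have two levels, so the exact number depends on how many size categories are used.

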### Measures

Researchers will help the parents/caregivers complete a baseline questionnaire collecting information on COHRQoL using the Early Childhood Oral Health Impact Scale (ECOHIS) for children ≤6 years old [28]. The scale has been evaluated for Australian children and found to have acceptable reliability and validity [29]. We will also collect parent fear levels using the Index of Dental Fear and Anxiety [30] and child dental fear as reported by the parents as well as self-report by children ≥3 years old using the faces scale [31]. Changes in health utility will be evaluated using the generic Child Health Utility 9D Index (CHU_9D) [32], the Euroqol 5D Youth (EQ-5D-Y), and the new oral health specific utility scale planned to be developed in this study. The ECOHIS has been used successfully among Australian Aboriginal population by author LJ in her National Health and Medical Research Council (NHMRC)‒supported research on pregnant Aboriginal women, while the other measures have been used among disadvantaged populations. We will also evaluate the validity of the questionnaires used among this population.

Participant involvement in the proposed study is shown in Table 1. Both test and control groups will complete the same questionnaire on COHRQoL, child dental fear, the CHU_9D, and the EQ-5D-Y, one month after treatment. The test and control groups will also complete the childhood oral health‒related questionnaire and the CHU_9D and the EQ-5D-Y, at the one-month posttreatment, but anchoring their responses to what their child’s oral health was like before the treatment (“Then-test”) to evaluate the possible effects of response shift [33]. Questionnaires on COHRQoL and parent/child fear and anxiety will again be collected at the 12-month follow-up.

We anticipate the clinical examination to take about 10 minutes, and completion of the questionnaire about 30 minutes. ART-based treatment times will vary depending on the extent of treatment required. Treatments may involve multiple appointments, usually about 20 minutes at each appointment. A sample of study participants will be invited to focus group interviews, which will take approximately 1 hour per group.

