### Sample Size

A recently completed pilot study in WA, which compared ART-based care against standard care, reported a nine-fold difference in the proportion of children referred for specialist pediatric dentist care (5% vs 49%). A conservative difference in effect size of 2.5 was assumed to estimate the sample size (10% vs 25%). The intracluster correlation was estimated from the dental caries experience of Aboriginal children participating in a NHMRC Project Grant (1010758)‒funded cluster randomized trial (.05). Using these parameters, with 15 clusters available in each arm of the trial, the estimated sample size required, at 80% power and alpha of .05, was 165 in each arm of the trial with 11 children per cluster. Allowing for loss to follow-up of 25%, the estimated sample size is 220 per arm of the study or 15 children per cluster. The recently completed pilot trial in WA, undertaken by author PA, achieved 90% retention of study participants after 12 months, while an oral health promotion intervention undertaken by author LJ among an Aboriginal population achieved 80% retention of study participants. The estimated sample size will have sufficient power to detect a 33% difference in mean ECOHIS at 90% power and alpha of .05.

The study timeline is shown in Table 2. It is expected that community engagement will take the bulk of the first year in recognition of the challenges of undertaking research in northwestern WA, which is as far as Sydney is from Perth (about 3000 km). Participant recruitment and treatment provision is similarly expected to take up to 2 years because of constraints of locations of communities and weather conditions.

**Table 2 table2:** Study timeline, indicated by actions taken per quarter.

Action	Year 1				Year 2				Year 3				Year 4				Year 5			
	1	2	3	4	1	2	3	4	1	2	3	4	1	2	3	4	1	2	3	4
Community engagement, staff recruitment, training, ethics approval, printing	✓	✓	✓	✓																
Participant recruitment, baseline, examinations, randomization, commence treatment, baseline data entry			✓	✓	✓	✓	✓	✓	✓	✓										
Follow-up examinations, focus group interviews, delayed intervention group treatments							✓	✓	✓	✓	✓	✓	✓	✓	✓					
Data entry, data clean-up, data analyses									✓	✓	✓	✓	✓	✓	✓	✓	✓			
Report preparation, community presentation and feedback																	✓	✓	✓	✓

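### The secondary-outcome analysis lists Poisson regression under change outcomes that can be negative, and analyses change in ECOHIS although power was stated for the mean score; a baseline-adjusted 12-month score resolves both

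*Protocol article*

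**What the plan says.** The Data Analysis section of the protocol article opens the relevant sentence with its outcomes: "Changes in health utility and COHRQoL (secondary outcomes) will be tested using paired (within group) and unpaired (between groups"). The same sentence then gives the adjusted models: "multivariate analysis using linear regression for continuous variables and Poisson regression for count variables to control for possible intergroup imbalances". It does not say which variable is the count, which model ECOHIS goes to, or which covariates are used. The next sentences add that every analysis will respect the clustering.

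The Measures section identifies the quality-of-life instrument: "COHRQoL using the Early Childhood Oral Health Impact Scale (ECOHIS"). The article gives neither its item scoring nor its range. Table 1 shows it collected in both arms at baseline, at one month and at 12 months.

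The article alternates between change and level. Aim 4 sets out to measure change, but its hypothesis concerns level: "The child oral health-related quality of life in the test group will be better than the control". The Sample Size section also speaks of level, claiming "sufficient power to detect a 33% difference in mean ECOHIS at 90% power and alpha of .05".

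**The concern.** The grammatical subject of the sentence is changes, so both regression models act on changes. Health utility is continuous, which leaves ECOHIS as the only candidate for the count model. The more obvious count, caries increment, is a primary outcome under Aim 1, and the preceding sentence sends Aim 1 to tests of proportions and logistic regression. The Poisson clause therefore either acts on a signed change, where the Poisson likelihood is undefined for negative values, or acts on nothing.

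The second issue is that power is claimed for a difference in mean score while the analysis is of change. These two analyses have different variances, and the relation between them depends on the correlation between baseline and follow-up. At stake are the precision of the Aim 4 result and an open choice between a difference in points and a rate ratio, which should be settled before data are seen.

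**Working it through.** **Inputs from the Sample Size section.** 15 communities per arm, 11 children each (165 per arm), intracluster correlation 0.05, a 33% difference in mean ECOHIS, 90% power, alpha 0.05 (taken as two-sided). No ECOHIS mean, SD or correlation is given.

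**The plan's own sample size.** The two-proportion formula for 10% versus 25% at 80% power gives 100 per arm. The design effect is 1 + (11 − 1) × 0.05 = 1.5, so 150 per arm, or 150/11 = 13.6 communities, rounded up to 14. One further community per arm gives 15 × 11 = 165, and 165/0.75 = 220. The stated figures are reproduced.

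**The ECOHIS power claim.** It cannot be reproduced without a mean and SD, but the SD it implies can be found.
- Effective number per arm: 165/1.5 = 110.
- Detectable standardised difference: (1.960 + 1.2816) × √(2/110) = 0.437.
- Implied SD: 0.33/0.437 = 0.755 × mean.
- If clustering was ignored: (1.960 + 1.2816) × √(2/165) = 0.357, and the implied SD is 0.925 × mean.

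**Can the change be negative?** Yes, for any child who moves in the other direction. As an illustration, integer scores were simulated with assumed baseline means of 6 or 10, coefficients of variation of 0.75 or 1.0 and correlations of 0.3 or 0.6, with a 33% difference at follow-up. Improvement was negative in 22% to 41% of children.

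**Change against level.** Let σ be the SD at both times (assumed equal) and ρ the baseline to follow-up correlation, with the same design effect for each analysis. Variance per child:
- follow-up score alone: σ²
- unadjusted change: 2(1 − ρ)σ²
- follow-up adjusted for baseline: (1 − ρ²)σ²

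The ratio of adjusted to change variance is (1 − ρ²)/[2(1 − ρ)] = (1 + ρ)/2, that is 0.65 at ρ = 0.3 and 0.80 at ρ = 0.6.

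Stated 90% power for the follow-up mean corresponds to an effect of 1.960 + 1.2816 = 3.242 standard errors. Dividing by the relative SD and subtracting 1.960 gives the power:

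| Analysis | ρ = 0.3 | ρ = 0.6 |
|---|---|---|
| Follow-up mean (as stated) | 90% | 90% |
| Unadjusted change | 3.242/√1.4 = 2.740; 78% | 3.242/√0.8 = 3.624; 95% |
| Follow-up adjusted for baseline | 3.242/√0.91 = 3.398; 92% | 3.242/√0.64 = 4.052; 98% |

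The change analysis falls below the stated 90% when 2(1 − ρ) exceeds 1, that is when ρ is below 0.5. The adjusted analysis has at least 90% at any ρ.

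**If a count model is wanted.** With SD 0.755 × mean, variance divided by mean is 0.755² × mean = 0.57 × mean, or about 1.7, 3.4 and 5.7 at assumed means of 3, 6 and 10. A plain Poisson model on the 12-month score would therefore be overdispersed, and a community random intercept does not cover child-level overdispersion. Negative binomial is the safer count model.

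**The case against.** The strongest reply is that the sentence is a rule by variable type. Poisson is reserved for counts, a signed change is not a count, and linear regression in the same sentence accepts negative values. This stands. A reader might infer that the adjusted analysis of Aim 4 cannot be run as written, and the document does not support that. It also nowhere gives ECOHIS scoring, so treating the scale as an integer score is an assumption.

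A reader might also infer that forcing the change into a Poisson model would lose half or more of the effect. The article proposes no such workaround, and the claim is not generally true. In the simulation described above (165 per arm, no clustering), dropping negative changes kept 9% to 37% of the difference and setting them to zero kept 35% to 63%. Adding a constant kept all of it, and Poisson on the 12-month score with baseline as covariate returned rate ratios of 0.66 to 0.68 against a true 0.67.

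The linear regression may also include baseline ECOHIS among its covariates. If it does, the treatment coefficient for the change equals that for the 12-month score and no precision is lost. The article names no covariates, so this is possible but not stated.

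Finally, assigning models to variables is commonly left to the analysis plan, which is not shown. That covers missing detail. It does not cover a stated pairing of a count model with change outcomes, or a power claim for a different quantity from the one analysed.

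**Conclusion.** The point holds as a minor one. The Poisson clause has no valid outcome in the sentence where it stands, and the article states power for a mean score while planning to analyse change. A valid model, linear regression on the change, is available.

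The size is a matter of precision: baseline adjustment reduces the variance to between 0.65 and 0.80 of the unadjusted change analysis. Power is about 92% instead of 78% at a correlation of 0.3, and about 98% instead of 95% at 0.6. These figures assume that the stated 90% is for the follow-up mean, that the SDs at the two times are equal, that the design effect is the same for both analyses, and that the correlation lies in the range shown. The document supplies none of these. The outcome is secondary, and neither the primary analysis nor the 165 and 220 per arm is affected.

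**What to change.** In the Data Analysis section, name the 12-month ECOHIS score as the outcome for Aim 4. Analyse it with a linear mixed model that has treatment arm, baseline ECOHIS and the randomisation strata (community size and baseline caries experience) as fixed effects and a random intercept for community. If a ratio effect is preferred, specify a negative binomial mixed model on the 12-month score instead, and choose between the two before data are seen. Keep count models for non-negative counts only. In the Sample Size section, say that the 33% difference refers to the 12-month mean.

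The cost is a sentence or two of wording. Baseline and 12-month ECOHIS are already collected in both arms, so no new data and no extra participants are needed.
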